**Methods:**

This is a randomized controlled trial; 86 patients will be randomly assigned into two acupuncture treatment groups at a ratio of 1:1. The whole study period includes 2 weeks baseline, 2 weeks treatments, and 12 weeks follow-up (4 and 12 weeks after treatment). The pain severity, the neck disability index, the cervical range of motion, and the pressure pain threshold, etc., will be used to evaluate the clinical efficacy of two acupuncture prescriptions for NP treatment. The MRI scans will be performed to detect cerebral activity changes of 20 patients in each group. The clinical data and MRI data will be analyzed, respectively. *Pearson* correlation coefficient will be used to evaluate the association between changes of cerebral activity features and improvement of clinical symptoms.

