Advances in neuroimaging techniques have enhanced studies into the central mechanisms of acupuncture as an analgesic in vivo. In the last two decades, many neuroimaging studies have been performed to elucidate the mechanisms of acupuncture analgesia, and achieved gratifying results [15–18]. For example, an fMRI study on migraines found that acupuncture was effective in improving abnormally reduced functional activity in the rostral ventromedial medulla/trigeminocervical complex area of patients [19]. Recently, significant alterations in the brain structure and function of NP patients have been reported by neuroimaging studies. Compared to healthy subjects, NP patients shown decreased functional activity in the left sensorimotor cortex and right temporoparietal junction [20], as well as increased functional connectivity between the right dorsolateral prefrontal cortex and the right anterior insula, which are associated with pain intensity [21]. Based on these findings, neuroimaging techniques appear to be useful tools for investigating the central mechanisms of acupuncture therapy for NP. Therefore, by MRI, this study aims to (1) evaluate the therapeutic effects of different acupoints prescription on NP, (2) investigate the changes in cerebral activity elicited by acupuncture treatment, and (3) analyze the possible correlations between the improvement of clinical symptoms and changes in brain activity, so as to explore the potential central mechanism of acupuncture for NP.

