#### Sample size

This study aims to compare the difference of the clinical efficacy of two acupuncture prescriptions (group A and group B). According to the results of the pilot study, the average reduction of VAS score in group A was 2.86±0.99, and the average reduction of VAS score in group B was 2.14±0.99. According to the formula, $$ n=\frac{2{\sigma}^2}{{\left(\mu 1-\mu 2\right)}^2}\times {\left({\mu}_{\alpha /2}+{\mu}_{\beta}\right)}^2 $$, with *α* = 0.05 (both sides) and 1 − *β* = 0.80 [24]. The sample size of each group was calculated to be 34, considering a 20% dropout rate; the final sample size was set to 43 per group, making the total of 86 in this study.

There is no widely accepted method for sample size calculation in neuroimaging study. Referring to the previous study [25], 15 participants in each group are the smallest size in neuroimaging studies. Considering a 20% dropout rate and the unavailability of data due to various reasons, this study will randomly select 20 patients from each group for MRI scans.

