### Data analysis

#### Clinical data analysis

The comprehensive effectiveness analysis will use the per protocol set (PPS) and the full analysis set (FAS). The FAS population will be used as the primary population for all efficacy analyses. The safety set (SS) included all subjects who received at least one treatment after randomization. When the results of PPS analysis and FAS analysis are inconsistent, PPS and FAS are discussed separately to find out the reasons for the inconsistency. Missing data will be handled using the last-observation-carried-forward (LOCF) method.

Statistical analysis will be conducted using SPSS 26.0 (IBM, Chicago, IL, USA) statistical software. *P* < 0.05 (two-sided) is considered statistically significant. Quantitative data are described with mean ± standard deviation (SD). Qualitative data are described with frequency and percentage (*N*, %). Student’s *t-*test and chi-square test will be used to compare the differences between groups at baseline. The assessment of the difference between the two groups will use repeated measures analysis of covariance (ANCOVA), taking into account the baseline values of age, sex and disease duration as covariates. Clinical data on skewed distribution will be compared using a non-parametric test.

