#### BOLD-fMRI data analysis

The fMRI data preprocessing and comparison will be performed using SPM12 software (http://www.fil.ion.ucl.ac.uk/spm/) based on MATLAB 2018a (Mathworks, Inc., USA). The steps including: format conversion, slice timing correction, head motion correction, spatial standardization, linear trend removal, spatial smoothing, and band-pass filtering. After pre-processing, the amplitude of low frequency fluctuation and regional homogeneity will be calculated to reflect the local cerebral functional activity, and the seeds-based functional connection analysis will be performed to reflect the functional integration of the brain. ANOVA will be used for comparisons between the two groups, with multiple comparison corrections.

Furthermore, the *Pearson* correlation analysis will be conducted to assess the associations between the changes of fMRI and the improvement of clinical symptoms.

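### The brain-symptom analysis is a Pearson correlation with no arm term, no statement on pooling and no stated correction for its tests, so arm differences or test count could pass for mechanism

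*Protocol article*

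**What the plan says.** The BOLD-fMRI data analysis section names three imaging measures: amplitude of low-frequency fluctuation, regional homogeneity and seed-based connectivity. On the group comparison it says: "ANOVA will be used for comparisons between the two groups, with multiple comparison corrections". A separate paragraph then adds that a Pearson "correlation analysis will be conducted to assess the associations between the changes of fMRI and the improvement of clinical symptoms". The Methods part of the Abstract repeats the choice: a Pearson "correlation coefficient will be used to evaluate the association between changes of cerebral activity features and improvement of clinical symptoms".

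Neither place mentions arm, pooling or covariates for this correlation, and neither says which clinical measures or brain regions enter it. By contrast, the Clinical data analysis section gives the group comparison of clinical outcomes named covariates (age, sex, disease duration). That section sets the significance level: P < "0.05 (two-sided) is considered statistically significant".

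The Background gives the purpose of the correlation. Its third aim is to "analyze the possible correlations between the improvement of clinical symptoms and changes in brain activity, so as to explore the potential central mechanism".

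**The concern.** A Pearson coefficient computed over both arms mixes two things: the association between patients within an arm, and the difference between arm means. Only the first says that patients whose brain activity changed more also improved more. The second appears whenever the arms differ on both variables, whether or not the two are linked in any patient. This trial is sized on an arm difference in VAS reduction, so half of that condition is built into the design.

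The number of tests is a distinct matter and would remain with no arm difference at all. There are three imaging measures and up to eight clinical ones, and the only correction mentioned sits with a different analysis.

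What is at stake is the mechanistic reading. The Discussion hypothesises that acupuncture relieves neck pain by modulating brain activity. A correlation produced by arm membership, or by the number of correlations tried, would be read as support for that.

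**Working it through.** The protocol gives no figure for the correlation, so there is none to reproduce. The check uses the plan's own inputs and shows assumed values as ranges.

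**Inputs from the protocol**
- VAS reduction (Sample size): "the average reduction of VAS score in group A was 2.86±0.99" and "the average reduction of VAS score in group B was 2.14±0.99". The standardised difference is d_y = (2.86 − 2.14)/0.99 = 0.72/0.99 = 0.727.
- Scanned patients (Sample size): 20 per arm, 40 in all. With the plan's 20% dropout, 16 per arm.
- Two-sided level 0.05 (Clinical data analysis).
- Three imaging measures (BOLD-fMRI data analysis). Eight clinical measures (Outcomes): VAS, NDI, SF-36, SAS, SDS, ROM, PPT and musculoskeletal ultrasound.

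**Assumed:** the standardised arm difference in brain change, d_x, from 0.5 to 1.5; zero association within each arm; normal data.

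**Step 1. Correlation induced by arm alone.** With equal arms and no within-arm association, the pooled correlation is

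r = (d_x·d_y/4) / √[(1 + d_x²/4)(1 + d_y²/4)].

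For d_x = d_y = 0.727: numerator 0.1322, denominator 1.1322, r = 0.117. For d_x = 1.0: 0.1818/1.1897 = 0.153. If the arm with the smaller VAS reduction has the larger brain change, d_x is negative and so is r.

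**Step 2. False-positive rate.** Simulation, 100,000 runs per setting:

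| Assumed d_x | Induced r | Pooled, 20 per arm | Pooled, 16 per arm | Adjusted for arm, 20 per arm |
|---|---|---|---|---|
| 0 | 0.00 | 5.0% | 4.9% | 4.9% |
| 0.5 | 0.08 | 8.0% | 7.4% | 5.0% |
| 0.727 | 0.12 | 11.1% | 9.9% | 5.0% |
| 1.0 | 0.15 | 15.7% | 13.3% | 5.0% |
| 1.5 | 0.21 | 25.3% | 20.8% | 5.1% |

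A Pearson test within one arm also stays at about 5%. For scale, the critical |r| is 0.31 with 40 patients and 0.44 with 20.

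**Step 3. If regions are chosen for a group difference.** Suppose a region is carried into the correlation only when its arm difference has p < 0.001 (an assumed threshold). Among the regions selected, the pooled false-positive rate at 20 per arm is about 20% at a true d_x of 0.5, 21% at 0.727, 23% at 1.0 and 27% at 1.5. Adjusting for arm again gives about 5%. Selection makes the observed brain difference large even where the true one is modest.

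**Step 4. Number of tests.** With k independent tests at 0.05 and no true association, the chance of at least one false positive is 1 − 0.95^k.
- VAS alone, three imaging measures: 1 − 0.95³ = 14.3%.
- All eight clinical measures: k = 3 × 8 = 24, 1 − 0.95²⁴ = 70.8%.
- Run separately in each arm, VAS alone: k = 6, 1 − 0.95⁶ = 26.5%.

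These counts take one region or seed per imaging measure; the number of regions and seeds is not stated.

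**The case against.** The strongest reply is that the protocol never says the arms are pooled. A Pearson correlation within each arm has no arm artefact. Pooling, covariates and the family of tests are also details that a journal article often leaves to an analysis plan. This stands in part. A reader might infer that the plan ignores arm, but the text does not support that; it is silent, and the inflation in Steps 1 to 3 is conditional on pooling. The reply does not remove the point, because the article does name the method, and neither reading of it is satisfactory. Pooled, it is open to confounding by arm. Per arm, it rests on 20 patients and doubles the tests, with no correction stated for them.

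Four further limits also stand.
- A reader might infer that regions found by the ANOVA feed the correlation and so differ by arm by construction. No such selection step is described; regions could equally come from predefined seeds or from pre-post change. Step 3 shows only what would follow if it were used.
- The arm effect needs a difference in brain change as well as in VAS. At a brain difference equal to the plan's VAS effect it is moderate: 11%, with an induced r well below the critical value.
- The 71% is an upper illustration for 24 tests. Clinical scores from the same patients, and imaging measures from the same scan, are correlated, which would normally lower it, and the plan does not say that all 24 would be run. The correction named beside the ANOVA might also be meant to cover the correlations, although the wording does not say so.
- The third aim is already worded cautiously, as exploring possible correlations, and the mechanism question draws on the imaging comparisons too.

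**Conclusion.** The concern holds in a conditional form, as two separate problems.

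First, if the arms are pooled and brain change differs by arm, an unadjusted Pearson correlation can be significant with no association inside either arm. Its false-positive rate is about 8% to 25% for assumed brain differences of 0.5 to 1.5 SD, and about 20% to 27% if regions are first selected for a group difference at an assumed p < 0.001, against a nominal 5%. This rests on the plan's pilot VAS difference of 0.73 SD and 20 analysable scans per arm. If the arms do not differ in brain change, the rate is 5%.

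Second, if the correlations are left uncorrected, the chance of at least one false positive runs from 14% (three imaging measures against VAS alone) to about 71% (24 tests, independence assumed).

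Neither problem causes the other, and neither affects the clinical efficacy comparison. The documents do not show that the analysis will be pooled or uncorrected. They show that the stated method does not rule out either, in the analysis meant to speak to mechanism. That warrants a change of wording before the imaging data are analysed.

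**What to change.** In the BOLD-fMRI data analysis section, and in the Abstract to match:
- Replace the plain Pearson correlation with a partial correlation adjusted for arm, or a regression of symptom change on fMRI change with an arm term.
- Report the estimate within each arm with its 95% confidence interval.
- Name VAS change, already the primary outcome, as the key clinical variable.
- List the correlations to be tested and how their regions or seeds are chosen, and extend false discovery rate control to that set.
- Label the result exploratory.

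The cost is a few lines of text, one degree of freedom for arm, and fewer nominally significant correlations. No new data or change in conduct is needed. Baseline VAS and mean head motion could be added as covariates, but this point does not depend on them.

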## Discussion

To the best of our knowledge, this is the first randomized controlled study to investigate the clinical efficacy and underlying mechanisms of different acupuncture prescriptions for NP. The results of this study are beneficial for the prescription selection of acupuncture for treating NP and elucidate on the mechanisms of acupuncture for NP.

### Selection of acupoint prescription

Many clinical studies have been performed on acupuncture for NP, and its efficacy has been identified. In clinical practice, the combination of local and distal points is a basic principle of acupoint prescriptions, but the number of prescriptions and acupoints involved is enormous. Therefore, in this study, two different prescriptions will be selected to compare their efficacy and possible mechanisms. Neck tenderness point will be selected as the basic acupoint, which is the most commonly used local acupoint in NP treatment. LU7 and LU5, located in the forearm, will be selected as the distal points in group A. These two points are the effective and common acupoints for neck diseases based on the traditional Chinese medicine theories and clinical practice [33–35]. HT4 and HT3, also located in the forearm, will be selected as the distal points in group B. These two acupoints are located on the same nerve segment as those in group A. This is a commonly available method for determining a control group in acupuncture studies and has been proven to be effective in blinding patients in many studies [36, 37].

### The combination of subjective and objective outcome measures

Pain is an unpleasant sensory and emotional perception that is associated with actual or underlying tissue pathology [38]. Human behavior, psychological, and social factors play a crucial role in the long-term maintenance of pain [39]. Therefore, the multidimensional nature of pain requires that the measurement of NP should include both subjective outcomes and objective outcomes. In this study, subjective outcomes including VAS, NDI, SAS, and SDS will be used to assess pain perception, dysfunction, and emotional state of the patients. Objective outcomes such as tenderness threshold, musculoskeletal ultrasound, and ROM will be used to evaluate the symptom improvement in the NP patients. The combination of subjective and objective outcomes can be more complementary to assess the efficacy from multiple perspectives and reduce the occurrence of potential bias, so as to improve the quality of clinical evidence.

### Application of neuroimaging technology

Previous neuroimaging studies have demonstrated that patients with NP exhibit abnormalities in brain activity and structure. For example, Chen et al. [40] found increased spontaneous brain activity in the supplementary motor area of NP patients and subsequently suggested a correlation between abnormality of the salience network with the disease. Another single fMRI-based case control study associated NP with activation and/or recall of pain memory [41]. Elsewhere, a voxel-based morphometry study performed on NP patients revealed the loss of bilateral clusters of gray matter in the sensorimotor cortex and pulvinar nucleus with NP pathophysiology [42].

Moreover, it has been reported that central integration is the key determinant of the effectiveness of acupuncture [43]. With previous studies, performed on individuals with shoulder pain [44], fibromyalgia [45], and low back pain [46], as well as knee osteoarthritis [15] indicating that regulation of brain activity might be an important factor influencing acupuncture’s modulating effects on pain. For example, acupuncture has been shown to effectively reduce pain by modulating brain regions related to both sensory-discriminative and emotional aspects [47]. Such regions were found to be important for the therapeutic effects of acupuncture on NP [40]. Based on these evidences, we hypothesize that acupuncture can effectively treat NP by modulating alteration of brain activity.

This trial is the first study to use fMRI to explore the central mechanisms of different acupuncture prescriptions in the treatment of NP. The results of this trial will help to provide visualization evidence for the clinical application of acupuncture for NP treatment.

### Trial status

The trial is currently in the recruitment phase and the study is expected to end in December 2021.

## Data Availability

Not applicable.

## Abbreviations

3D-T1WI: Three-dimensional T1-weighted imaging
ANCOVA: Analysis of covariance
BOLD-fMRI: Blood oxygenation level-dependent fMRI
RS-fMRI: Resting state functional magnetic resonance imaging
CRF: Case report form
DTI: Diffusion tensor imaging
FA: Flip angle
FAS: Full analysis set
FDR: False discovery rate
FOV: Field of view
GLM: General linear model
HbO: Oxygenated hemoglobin
HbR: Deoxygenated hemoglobin
LOCF: Last observation carry-forward
MRI: Magnetic resonance imaging
MSUS: Musculoskeletal ultrasound
NDI: Neck disability index
NP: Neck pain
NIH: National Institutes of Health
PPS: Per protocol set
PPT: Pressure pain threshold
ROM: Range of motion
SD: Standard deviation
SF-36: Short-form 36-item Health Survey
SAS: Self-Rating Anxiety Scale
SDS: Self-Rating Depression
SS: Safety set
TCM: Traditional Chinese medicine
TE: Echo time
TR: Repetition time
VAS: Visual analogue scale
